### Randomisation and blinding

Participants will be stratified by sex and block-randomised in random concealed block sizes of 3 to 12 (1:1:1) in three parallel groups. A researcher not involved in the trial generated the allocation sequence using a random number generator on www.sealedenvelope.com and is the only person who knows the block sizes. The researcher was trained by the project manager in generating allocation sequences, and the process was piloted.

The randomisation is coded so that the project manager does not know which intervention is linked to which group number (group 1, 2 or 3). The envelopes will be kept in a locked room at Aalborg University Hospital where only the two physiotherapists involved in baseline testing have access. The randomisation schedule was prepared at the Center for General Practice at Aalborg University by a person not involved in the actual trial. The notes in the envelopes state both group number and intervention, and the physiotherapists responsible for assessing participants and delivering the interventions will not be aware of the coding before they open the first envelopes. In practice, after a participant has been enrolled, has filled out questionnaires, and has received initial patient advice and information regarding the practicalities of participation, the physiotherapist will take an envelope and assign the participant to the allocated treatment on the basis of randomisation.

The project manager will be responsible for performing the statistical analyses and will remain blinded to the coding until after the analyses have been performed. The analyses will be performed after the examination that includes the primary endpoint (the 12-week follow-up) of the last participant.

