### Statistical analyses

All statistical analyses will be performed by a blinded data analyst according to a pre-established analysis plan using the intention-to-treat principle. This plan is written in consultation with a statistician and will be published on the Aalborg University website before the inclusion of the last participant. SPSS software (IBM Corporation, Armonk, NY, USA) will be used as statistical software. We will use Q-Q plots and histograms to assess data normality. Missing outcome data will be imputed using multiple imputations based on the values from previous follow-ups, sex, age, and group allocation.

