#### Primary analysis

The primary analysis will investigate the between-group difference in FHSQ pain. We will use a linear mixed effects model with the participant as a random effect, and time (4, 12, 26 and 52 weeks), group allocation (PA or PAX or PAXI) and baseline value as fixed effects. Conclusions will only be drawn on the basis of the primary endpoint (12 weeks).

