### Trial status

Recruitment was started on January 21, 2019, and the first participant was included on February 7, 2019. No amendments have been made to the protocol (version 2.0 January 14, 2019) since it was pre-registered with ClinicalTrials.gov. When this protocol was submitted for publication (October 5, 2019), a total of 96 participants had been included in the trial. We expect recruitment to be completed in July 2020.

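### The analyses are timed at the last 12-week visit, but the primary model includes 26- and 52-week scores that many participants will not yet have

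*Protocol article*

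**What the plan says.** Under Randomisation and blinding, the protocol article gives a single timing rule: "The analyses will be performed after the examination that includes the primary endpoint (the 12-week follow-up) of the last participant". The same paragraph says that the project manager, who does the analysis, "will remain blinded to the coding until after the analyses have been performed".

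Under Primary analysis, the linear mixed model carries a random effect for each participant, and its fixed part is listed thus: "time (4, 12, 26 and 52 weeks), group allocation (PA or PAX or PAXI) and baseline value as fixed effects". No group-by-time term is listed. The section then says: "Conclusions will only be drawn on the basis of the primary endpoint (12 weeks").

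Under Statistical analyses, the missing-data rule is: "Missing outcome data will be imputed using multiple imputations based on the values from previous follow-ups, sex, age, and group allocation".

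Under Secondary analyses, risk differences for acceptable symptom state are planned at 12, 26 and 52 weeks. The article describes no second analysis time. Trial status gives the first inclusion as 7 February 2019, says that at submission on 5 October 2019 "a total of 96 participants had been included in the trial", and expects recruitment to finish in July 2020. Sample size sets the total at 180.

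**The concern.** When the last participant attends at 12 weeks, that person cannot have a 26- or 52-week score, and neither can anyone else enrolled late. The stated model therefore cannot be run on complete data at the stated time. The reader is left with two possible primary analyses. In one, the general imputation rule fills in visits that have not yet occurred. In the other, those visits stay empty and the model uses whatever later scores happen to exist.

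This matters because the trial expects effects to change over time: the Background and Discussion describe short-lived relief from the injection and a slower benefit from exercise. A single group effect averaged over visits then depends on which visits are in the data. The primary result could be reported at 12 weeks and take a different value when the same model is rerun a year into follow-up.

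Two related wordings need attention. The blinding sentence ties the end of blinding to the same analyses, so it can be read as ending before the long-term data are complete. The imputation rule uses earlier visits only, so a missed 12-week score would not draw on an observed 26- or 52-week score.

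**Working it through.** The article gives no figure for how much follow-up will be complete at the analysis, so there is no stated value to reproduce. The sample size is not affected by this point.

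**Step 1: who is not yet due.** At last inclusion + 12 weeks, the week-26 score is not due for those enrolled in the last 26 − 12 = 14 weeks of recruitment. The week-52 score is not due for those enrolled in the last 52 − 12 = 40 weeks.

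**Step 2: accrual.** Assume even accrual within each of two periods.
- 7 February to 5 October 2019: 240 days = 34.3 weeks; 96 / 34.3 = 2.80 per week.
- 5 October 2019 to the end of recruitment: 180 − 96 = 84 participants. An end on 1 July 2020 gives 270 days = 38.6 weeks, 2.18 per week. An end on 31 July gives 300 days = 42.9 weeks, 1.96 per week.

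**Step 3: counts not yet due.**

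| Recruitment ends | Week 26 | Week 52 |
|---|---|---|
| 1 July 2020 | 14 × 2.18 = 30.5 (16.9%) | 84 + (40 − 38.6) × 2.80 = 88.0 (48.9%) |
| 31 July 2020 | 14 × 1.96 = 27.4 (15.2%) | 40 × 1.96 = 78.4 (43.6%) |

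**Step 4: sensitivity to the accrual shape.** Uniform accrual over the whole period (510 to 540 days, or 72.9 to 77.1 weeks), ignoring the count of 96, gives 14/77.1 to 14/72.9 = 18-19% for week 26 and 40/77.1 to 40/72.9 = 52-55% for week 52.

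**Step 5: the pooled group effect if visits not yet due are left empty.** Take the model as listed (time, group, no interaction), equal visit patterns in the groups, and a common correlation ρ between visits. A participant with the first k visits observed contributes 1/(1 + (k − 1)ρ) to the weight of each of those visits. With ρ = 0.5 (an assumption) that is 0.4 for four visits, 0.5 for three and 0.667 for two.
- End on 1 July: 92.0, 57.5 and 30.5 participants have four, three and two visits due. Weights: weeks 4 and 12 each 92.0 × 0.4 + 57.5 × 0.5 + 30.5 × 0.667 = 85.9; week 26 = 65.6; week 52 = 36.8; total 274.1. The week-12 share is 85.9/274.1 = 0.313.
- End on 31 July: 101.6, 51.0 and 27.4 participants. Weights 84.4, 84.4, 66.1 and 40.6; total 275.6. The week-12 share is 0.306.
- All visits complete: 0.25 each.

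For illustrative true effects at weeks 4, 12, 26 and 52:

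| True effects | At the 12-week lock | At the end |
|---|---|---|
| 0, 14.1, 0, 0 | 4.3-4.4 | 3.5 |
| 0, 0, 14.1, 14.1 | 5.3-5.5 | 7.05 |
| 7, 14.1, 10, 7 | 9.9 | 9.5 |
| 14.1 at every visit | 14.1 | 14.1 |

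Correlations of 0.3 and 0.7 change these by about 0.1 or less.

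**Step 6: the same model with a group-by-time term.** The week-12 contrast comes back as 14.1 in the first row at both times, and equals its true value in every row.

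**Step 7: if visits not yet due are imputed as the rule says.** In a large-sample simulation with imputation from earlier visits and group (ρ = 0.5, age and sex omitted), the pooled effect at the lock was about 3.5 when the 14.1 effect was at week 4 only (final value 14.1/4 = 3.5). It was about 7.2 when the effect was at weeks 26 and 52 only (final value 7.05). The drift in Step 5 disappears, but nearly half of the week-52 values behind the result would then be imputed.

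**The case against.** The strongest reply is that the 12-week visit may be only an earliest date, and that a published analysis plan, promised before the last inclusion, is the usual place for lock dates and for handling visits not yet due. That is fair as to detail. It does not remove the conflict in what the article states: the only trigger named is the last 12-week visit, and the model and imputation rule given beside it do not fit that trigger.

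Several stronger readings are tempting, and the documents do not support them.
- *The primary result will be seriously biased.* Scores not yet due are absent because of enrolment date, so a likelihood-based model is not seriously biased by their absence. With a group-by-time term the week-12 contrast is unaffected. Whether a pooled effect suits a 12-week endpoint is a separate question.
- *The result both rests on imputed future visits and drifts.* Steps 5 and 7 show that these are alternatives. The drift arises only when those visits are not imputed and no interaction is fitted.
- *The drift is large.* It depends on the profile: nil for a constant effect, about 0.4 for the week-12-peaked profile, just under 1 point for an effect at week 12 only, and larger for purely late effects.
- *Blinding is lost for all long-term outcomes.* The article does not say that the codes are broken after a first run. This is an inference from the wording. The later questionnaires are also sent to participants by e-mailed link, and the project manager has no contact with them after referral.

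**Conclusion.** The concern holds as an internal inconsistency that should be resolved. The timing rule, the four-visit primary model and the unrestricted imputation rule cannot all be followed as written without either imputing visits that have not happened or fitting a pooled effect whose visit weights change later. The size is 15-17% not yet at week 26 and 44-49% not yet at week 52, rising to 18-19% and 52-55% under uniform accrual. These are projections from the dates in Trial status and depend on the accrual shape and on a July 2020 finish. The pooled-effect figures further assume ρ = 0.5, no imputation and no group-by-time term. The end of blinding before the 26- and 52-week data are complete is a possible reading that the text should rule out, not a stated step.

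**What to change.** Reconcile the timing, model and imputation statements by naming two locks.

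- **12-week lock.** Fit weeks 4 and 12 only, with group-by-time. Report the week-12 contrast as the final primary result. Impute nothing for visits not yet due.
- **52-week lock.** Analyse weeks 26 and 52 as secondary. Either keep the group codes blind until then, or freeze the scripts before the first unblinding.
- **Imputation, if kept.** Impute scores that were due but missed from all observed visits, later as well as earlier. At the 12-week lock, any later scores already in hand serve as predictors in the imputation only, not as outcomes in the primary model.

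The cost is wording and one extra frozen script. No data collection changes.

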### Interventions

#### Patient advice and heel cup

Participants in all three groups will receive the same initial fundamental patient advice and leaflet about their condition before randomisation. They receive brief information about pathology, risk factors and advice on how to decrease activities that lead to symptom flares and slowly progress back to former activity levels guided by symptoms. To ensure that all participants receive the exact same information, the physiotherapists read a written information out loud; however, they will ask control questions to clarify if the participants understand the information and allow participants to pose questions about the information and participation in general. The leaflet includes the same information that the physiotherapists deliver orally after inclusion in the trial.

Participants will be asked to refrain from seeking other treatments during the course of the trial. They will be allowed to self-treat their PF for pain relief (e.g., with ice or heat packs, rolling a tennis ball under the heel, or massaging the plantar fascia) if they have been doing this for at least 4 weeks prior to inclusion, but they will not be encouraged to do so. Participants will be handed a project diary in which they are asked to record any treatment that they may have received during the course of the trial, including any type of self-treatment and use of analgesic or anti-inflammatory substances. We will inform participants that follow-up on outcomes is critical, regardless of whether they comply with their allocated treatment. Two weeks after inclusion, the physiotherapist who included the participant will contact the participant to ask if they have any questions regarding the condition, the practicalities of participation, or in relation to performing the exercise depending on randomisation. If participants have not achieved a self-evaluated satisfactory result after 12 weeks, they may discuss other evidence-based treatments (e.g., plantar fascia stretching) with the physiotherapist, but they will be encouraged to continue to comply with their allocated treatment.

We will give all participants a silicone heel cup (Medi-Dyne Healthcare Products, Colleyville, TX, USA) for each shoe, and they are advised to use the heel cups whenever they are wearing shoes. If participants already use an insole or another type of foot orthosis, they are allowed to continue wearing this if they prefer this over the heel cups.

#### Heavy-slow resistance training

Participants of the PAX and PAXI groups will be instructed in performing a heel-raise exercise standing with the forefoot on a step or a book as per Rathleff et al. [26]. Unlike the pre-determined programme used in that trial, we will use a self-dosed programme that we recently found to be associated with the same level of improvement as the pre-determined programme [16]. Participants will be told that it is important that the exercise be performed with an adequately heavy load, and they will be instructed in performing the heel raise with a load corresponding to an 8 repetition maximum (RM) (i.e., a weight that can only be lifted eight times). They may only use a lower relative load if they feel they are unable to perform the exercise with 8 RM. They shall perform the exercise for as many sets as possible. The exercise descriptors are elaborated in Table 1. If participants feel they are able to perform more than eight repetitions with only their body mass (8 RM), an external load consisting of a backpack with books, weights or water bottles to add weight must be used. We will tell participants that pain during the exercise is expected and that there is no upper limit of pain they are allowed to experience, as long as they feel it is tolerable. Participants randomised to also receive the injection will be asked not to perform the exercise within 24 h from the injection and not to progress the method used to achieve 8 RM until 2 weeks after the injection. If heel raise without a backpack is sufficient to achieve 8 RM before the injection, participants should not perform the exercise with a backpack until the third week after the injection, regardless of any pain reduction following the injection. They will be told to perform the exercise until they achieve their Patient Acceptable Symptom State (PASS) (please see ‘Secondary outcomes’ section for elaboration) and an additional 4 weeks. To support the exercise execution, participants receive a written exercise instruction that also includes pictures of the exercise (Fig. 1).

**Table 1 Tab1:** Exercise descriptors

1. Load magnitude	8 repetition maximum
2. Number of repetitions	≥ 8 depending on the load
3. Number of sets	As many as possible
4. Rest between sets	2 min
5. Number of exercise interventions	Every other day
6. Duration of the experimental period	8 weeks
7. Fractional and temporal distribution of the contraction modes per repetition and duration (in s) of one repetition	3 s concentric 2 s isometric 3 s eccentric
8. Rest between repetitions	No
9. Time under tension	8 s/repetition ≥ 64 s/set ≥ 64 s/training session
10. Volitional muscular failure	Yes
11. Range of motion	Full range of motion
12. Recovery time between exercise sessions	48 h
13. Anatomical definition of the exercise (exercise form)	The participant stands with the forefoot on a step. The toes are maximally dorsally flexed by placing a towel underneath them. The participant performs a heel raise to maximal plantar flexion in the ankle joint and afterwards lowers the heel to maximal dorsal flexion. Supporting oneself for balance by placing the hands on a wall or a rail is allowed.

**Fig. 1 Fig1:**
[figure not shown]
Pictures of the exercise participants receive embedded in the written exercise instruction

#### Ultrasound-guided corticosteroid injection

Participants randomised to PAXI will receive an ultrasound-guided corticosteroid injection, preferably within 8 days from baseline but no later than 14 days after baseline. A 21-gauge, 40-mm needle is connected to a 2.5-cm^3^ syringe filled with 1 ml of triamcinolone acetonide 20 mg/ml (Trica; Evolan Pharma, Danderyd, Sweden) + 1 ml of lidocaine 10 mg/ml (Xylocaine; AstraZeneca, Wilmington, DE, USA). The skin is cleansed with chlorhexidine alcohol 0.5% (Medic, Jacksonville, FL, USA). The needle is inserted with a medial approach under ultrasound guidance aligned with the long axis of the ultrasound transducer. The injection is distributed deep and superficially on the plantar fascia surface anterior to the insertion on the calcaneal bone in the region of maximal fascia thickness (see Fig. 2).

**Fig. 2 Fig2:**
[figure not shown]
Ultrasound image of the calcaneus and the plantar fascia. The stars depict the placement of the injection

### Compliance

We will emphasise to participants that we do not know which of the three groups will be superior and that it is very important to comply with the group to which they are allocated for the future results to be meaningful. Participants in the PAX and PAXI groups will be told that complying with the exercise programme is very important and that exercise compliance is associated with the odds of their recovery. Complying with the exercise programme includes performing the exercise with the prescribed form, contraction time, and sufficient load and frequency. All participants will be asked to record their use of the heel cup and any other foot orthoses in a foot orthoses diary as an estimated percentage of the time they have worn shoes. In addition, participants performing exercise will receive a training diary in which they record the number of repetitions and sets and the date on which the exercise was performed.

### Variables

#### Descriptive

The assessment schedule is found in the SPIRIT figure (Fig. 3). During the telephone screening and the clinical examination, we will collect the following data: age, height, body mass index, location and duration of heel pain, average heel pain intensity during the past week (0 to 100-mm VAS, where 0 is no pain and 100 is worst heel pain imaginable), plantar fascia thickness measured by ultrasonography perpendicular to the calcaneal insertion, presence of palpable pain under the plantar heel, comorbidity, treatment history, previous care-seeking behaviour, if females are pregnant or breastfeeding, number of PF episodes, education level, and work status.

**Fig. 3 Fig3:**
[figure not shown]
SPIRIT figure. Schedule of enrolment, interventions and assessments

#### Primary outcome

The primary outcome is the mean pain domain score of the FHSQ at the 12-week follow-up. The FHSQ is a questionnaire ranging from 0 (worst possible score) to 100 (best possible score) with high reliability (ICC, 0.74–0.92) that assesses multiple dimensions of foot-related health and function and is recommended in this patient population [35, 36]. The minimal clinically important difference of the pain domain is 14.1 points [37]. We will use a Danish validated translation of the original questionnaire [38].

#### Secondary outcomes

Secondary outcomes include (1) the other domains of the FHSQ (function, footwear and general foot health domains), (2) Global Rating of Change (GROC), (3) PASS, (4) Pain Self-Efficacy Questionnaire (PSEQ), and (5) weekly light, moderate and vigorous physical activity levels.

We will use the GROC to measure participants’ self-reported improvement on a 7-point Likert scale ranging from ‘much improved’ to ‘much worse’. Participants are dichotomised as improved if they rate themselves as ‘much improved’ or ‘improved’ (categories 6 and 7) and categorised as not improved if they rate themselves from ‘slightly improved’ to ‘much worse’ (categories 1 to 5). PASS (yes/no) will be used as a measure of when participants achieve a self-evaluated satisfactory result and feel no need for further treatment. Therefore, this is not necessarily a measure of complete recovery, because some may be satisfied despite still experiencing symptoms. PASS has been used to evaluate clinically relevant states in PF and in other musculoskeletal disorders and post-operative pain [16, 39–41]. Participants will be asked to report to the physiotherapists as soon as they experience PASS, and the date will be noted. Furthermore, participants will be asked about their PASS status during follow-up. After the participant reports a PASS, they will be instructed to continue performing the exercise as prescribed for at least 4 weeks. The PSEQ measures pain self-efficacy and provides a score ranging from 0 (not at all confident) to 60 (completely confident), with lower scores indicating lower self-efficacy [42]. The Danish version of the PSEQ has been validated in a Danish chronic pain population and has high reliability (ICC, 0.89) [43]. To estimate weekly physical activity level expressed as metabolic equivalents (METs), we will use 3D accelerometry. Participants will be given a wrist-worn accelerometer (ActiGraph wGT3X-BT; ActiGraph LLC, Pensacola, FL, USA) during baseline and will be asked to wear this during the first 3 weeks after baseline and then return the accelerometer in a postmarked envelope. During the 12-week follow-up, participants receive the accelerometer again and will be wearing it for an additional 3 weeks before returning it. Participants will be instructed to wear the accelerometer at all times. We will use data from the first valid week recorded during the first and second rounds of wearing the accelerometer (i.e., 1 week during weeks 1 to 3 and 1 week during weeks 13 to 15). A valid week is defined as ≥ 4 days of ≥ 10 h of wear time [44]. Data will be extracted from the accelerometers using the ActiLife software.

